### Postoperative data collection and blinding

Prespecified study visits are carried out by clinical investigators and study nurses from the clinical study centre to collect information on the primary and secondary outcome parameters and to identify any postoperative complications.

Blinding of participants, research assistants, operating surgeons, data collectors and outcome assessors to the treatment allocation is not feasible. Postoperative blinding of patients, e.g. by the use of large dressings, is barely possible, since unblinding would occur when wound dressings were changed prior to the assessment of the primary endpoint. Furthermore, given the objective nature of the primary endpoint (morbidity according to the Clavien–Dindo classification), complex blinding interventions are not justified. In addition, numerous endpoints (economic parameters, safety endpoints, etc.) are independent of blinding. However, some secondary endpoints may be affected by the lack of blinding, e.g. pain or patient-reported outcomes such as quality of life or quality of recovery. Outcome assessments will be conducted by trained study personnel who are not part of the surgical or ward team, to guarantee objectivity. Data analysts will be blinded to the intervention.

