Rate of complete margin clearance in patients with malignant tumours	a. Microscopically complete margin clearance > 0.1 cm margin clearance, R0 (CRM−). b. Microscopic margin clearance ≤ 0.1 cm, R0 (CRM+). c. Microscopic margin involvement (R1) resections according to the 8th edition of the UICC TNM classification.
Lymph nodes in patients with malignant tumours	a. Number of lymph nodes resected. b. Number of tumour-positive lymph nodes.
Postoperative outcomes	
Mortality (%)	From the day of surgery until postoperative day 90.
Quality of recovery	Measured via the quality of recovery questionnaire QoR-15 [28], assessed at baseline and on POD 4.
Time to functional recovery (days)	Up to postoperative day 90; defined as: independently mobile at the preoperative level, sufficient pain control with oral medication alone, ability to maintain sufficient (i.e. > 50%) daily required caloric intake by mouth, no intravenous fluid administration and no signs of infection [29].
Total length of intensive care unit stay (days)	From the day of index operation up to postoperative day 90.
Length of hospital stay (days)	From the day of index operation up to the day of discharge.
Rate of superficial and deep surgical site infections (SSIs)	As defined by the Centres of Disease Control and Prevention (CDC) within 30 days [30]. Organ-space SSIs are excluded from this measurement as they are independent of surgical access, but rather depend on the underlying surgery. Consequently, organ-space SSIs will be recorded in the overall complication rate if applicable.
Pancreas-specific complications	Rate and severity within 90 days of: a. Postoperative pancreatic fistula as defined by the ISGPS [31]. b. Postpancreatectomy haemorrhage as defined by the ISGPS [32]. c. Delayed gastric emptying as defined by the ISGPS [33]. d. Biliary leak as defined by the ISGLS [34]. e. Chyle leak/lymphatic fistula as defined by the ISGPS [35].
Non-surgical re-interventions	Number of non-surgical re-interventions within 90 days after PD (e.g. image-guided drain placement, angiography with stenting/other interventions, endoscopy).
Re-operations	Number of re-operations within 90 days after PD.
Hospital re-admissions	Number of hospital re-admissions within 90 days after PD.
Pain	Pain scores at rest and during movement according to the Numeric Rating Scale (NRS) on POD 2 and 4.
Health-related quality of life (HRQoL)	Measured by the SF-36 at baseline, 30 and 90 days after index operation [36].

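### The statement that outcome assessors cannot be blinded makes no exception for reading the resection specimen, where its reasons do not apply and masking looks achievable at little cost

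*Protocol article*

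**What the plan says.** The section on postoperative data collection and blinding contains an unqualified statement: "Blinding of participants, research assistants, operating surgeons, data collectors and outcome assessors to the treatment allocation is not feasible". Four remarks in that section bear on it:

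- Masking patients with large dressings would fail, because "unblinding would occur when wound dressings were changed prior to the assessment of the primary endpoint".
- Further effort is judged unnecessary: "given the objective nature of the primary endpoint (morbidity according to the Clavien–Dindo classification), complex blinding interventions are not justified".
- Some endpoints are set aside: "numerous endpoints (economic parameters, safety endpoints, etc.) are independent of blinding".
- Others are conceded to be vulnerable: "some secondary endpoints may be affected by the lack of blinding, e.g. pain or patient-reported outcomes such as quality of life or quality of recovery".

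As safeguards, the section has outcomes assessed by trained staff from outside the operating and ward teams, and it keeps the data analysts blinded.

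Table 1 (definition of secondary endpoints) lists two oncological outcomes. One is "Rate of complete margin clearance in patients with malignant tumours", defined microscopically in three categories: clearance above 0.1 cm, clearance of 0.1 cm or less, and R1. The other covers lymph nodes: "Number of lymph nodes resected", and the number that are tumour-positive. The article does not say who reads the specimen or what that reader knows about the operation.

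**The concern.** The infeasibility statement is wider than the reasons given for it. Wounds and dressings reveal the approach to the patient and to anyone at the bedside. They do not reveal it to someone looking at a slide.

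A microscopic distance close to a 0.1 cm cut-off calls for judgement, and a node count depends partly on how thoroughly the specimen is searched. If the reader knows the approach, expectation can enter either assessment. The article's Background reports conflicting earlier results for margins and node yield, so a difference in EUROPA would be looked at closely. An unmasked reading would make such a difference harder to interpret, and that weakness looks avoidable.

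**Working it through.** The plan states no figure on this point, so the check sets the reasons and safeguards for not blinding against the specimen-based endpoints.

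1. **Dressing changes.** This reason concerns patients, and by extension staff who see the wound. It does not reach a specimen reader.
2. **Objectivity of the primary endpoint.** This reason concerns morbidity graded by Clavien–Dindo. It says nothing about margins or nodes.
3. **Endpoints independent of blinding.** Economic and safety endpoints are named and the list is left open. The oncological endpoints are not named.
4. **Endpoints affected by lack of blinding.** Pain and patient-reported outcomes are given as examples. Again the oncological endpoints are not named.
5. **Staff outside the surgical and ward teams.** This gives independence, not masking. An independent assessor can still know the allocation.
6. **Blinded analysts.** This protects the analysis but cannot undo a reading already made with knowledge of the approach.
7. **Other places in the article.** The section on methods for minimising bias has subsections on selection and attrition bias, and none on detection bias. Table 2 lists resection status with the intraoperative endpoints of the day of surgery and describes no separate masked reading.

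No reason given therefore explains why the specimen could not be read without knowledge of the approach.

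The two oncological endpoints differ in how far the point applies:

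- **Margins.** Table 1 states that the assessment is microscopic and has a cut-off. This is the stronger case.
- **Nodes.** Table 1 gives no method of assessment. The number resected also depends on the extent of lymphadenectomy, which the Interventions section leaves to the surgeon. Masking the reader would not remove that source of difference.

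**Size.** A bias estimate would need at least a rate of misreading and the difference in that rate between the groups. The documents give neither, so no bias can be calculated.

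**The case against.** The strongest objection is that unmasked specimen reading is nowhere stated. The section opens with the investigators and study nurses who carry out the visits, so the outcome assessors it means are most naturally those people. A pathologist is never mentioned. A condensed article may leave pathology procedures to the full protocol, which is available on request. Both lists of endpoints are also illustrative, so absence from them proves little.

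Much of this stands. A reader might infer that the plan rules out blinding for every assessor, the pathologist included, and that the oncological results will be biased. The documents do not support that: the sentence does not say so, and the reader's knowledge is simply not described. What remains is that the sentence makes no exception. If it means visit staff only, it should say so. If it includes the specimen reader, it is unsupported. Either reading calls for a correction.

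Two further inferences should be resisted:

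- **Cost justification.** It is tempting to say that oncological results here will decide whether the cost of RPD is justified. The Discussion assigns that question to a future confirmatory trial. The tasks it sets for EUROPA are willingness to be randomised and recruitment planning, the target population, and morbidity data for sample size.
- **Percentage points.** The share of malignant tumours is not given. If 50–80% of 32 patients per group is assumed, the denominators are 0.5 × 32 = 16 to 0.8 × 32 = 25.6. One reclassified specimen then moves a group's rate by 1/16 = 6.3 to 1/25.6 = 3.9 points. That is 1/n for any binary endpoint in groups of this size. It does not measure bias, and nothing in the documents suggests that errors would differ by group.

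**Conclusion.** The point holds in limited form. The infeasibility statement is broader than its reasons. Margin status, and node counts to a lesser degree, could be read without knowledge of the approach, and the article does not say whether they will be. Avoidable detection bias in these endpoints is possible but not shown, and its size cannot be computed from the documents.

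The consequence is small. These are secondary endpoints in the subgroup with malignant tumours, and the article describes all analyses as exploratory and descriptive. The CCI and its assessment are untouched. The conclusion assumes that the specimen can be handled and oriented without naming the approach; the article does not describe the pathology workflow, so the site should confirm this. The point is a cheap improvement of low priority.

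**What to change.** Limit the infeasibility statement to patients, surgeons and bedside or visit assessment. Then add wording such as: *Resection margins and lymph nodes are assessed without knowledge of the surgical approach. Specimens are sent with a request form that carries the trial number and the anatomical information needed for orientation, but not the approach. Any unmasking of the reader is recorded.* If masking is not possible at the site, give the reason instead.

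The cost is a short protocol change and a modified request form. On its face this needs no additional reader or procedure. The downside is that the reader may occasionally learn the approach through routine clinical contact. Recording those cases shows how far the masking held.

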### Description of trial visits

During the screening visit (1–14 days before surgery), inclusion and exclusion criteria are assessed (Table 2). After the patient has given informed consent, the demographic and baseline data, the ASA score, the updated Charlson Comorbidity Index [37], the health-related quality of life as measured by SF-36 [36], the quality of recovery as established using questionnaire QoR-15 [28] and the pancreas-specific medical history (indication for surgery, pre-existing diabetes mellitus, pre-existing exocrine insufficiency, neoadjuvant treatment, preoperative cholestasis, preoperative biliary drainage) are assessed and documented. Visit 2, including assessment of intraoperative and perioperative parameters as well as serious intraoperative complications, takes place on the day of surgery. Also documented during visit 2 are the type of pancreatic resection, extent of lymphadenectomy, additional organ resections, texture of the pancreas, size of the pancreatic duct at the transection site and drain insertion. Four inpatient follow-up visits on postoperative days (POD) 4, 8 and 12 and the day of discharge will be performed in person, and two telephone follow-up visits 30 and 90 days after surgery will be conducted to evaluate the primary and secondary outcome parameters (see Table 1). If a patient is discharged before POD 12, visit 5 can be omitted.

**Table 2 Tab2:** Trial visits

Visit	1	2	3	4	5	6	7	8
	1–14 days before surgery	Day of surgery (day 0)	POD 4	POD 8	POD 12	Day of hospital discharge	POD 30	POD 90
	Outpatient/inpatient	Inpatient					Inpatient/telephone	
Eligibility criteria	X							
Informed consent	X							
Baseline demographics and clinical data	X							
Randomisation	X							
Quality of life questionnaire (SF-36)	X						X	X
Quality of recovery (QoR-15)	X		X					
Intervention		X						
Serious intraoperative complications		X						
Intraoperative secondary endpoints (e.g. operation time, blood loss, conversion rate, resection status)		X						
Surgeon’s mental workload/stress		X						
Assessment of primary endpoint (CCI)			X	X	X	X	X	X
Postoperative secondary endpoints (e.g. re-interventions, pain, time to functional recovery)			X*	X	X	X	X	X
Procedure-related costs, all inpatient hospital costs								X

*POD* postoperative day

*Pain needs to be assessed on POD 2 and 4

### Statistics

#### Sample size calculation

Given that EUROPA is an exploratory trial, no formal sample size calculation was performed. However, a clinically relevant mean difference for the CCI is 10 [25, 26] while the mean standard deviation is approximately 20 in major abdominal surgery [38]. Including 64 patients (32 per group) in the analysis, this effect size could be estimated with a 95% confidence interval (CI) of [3.07, 16.93]. Considering that approximately eight patients per group will undergo neither RPD nor OPD due to inoperability or indication for another type of surgery (ascertained during the exploratory stage of the operation), a total of 80 patients will need to be allocated to the trial (Fig. 1).

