**Methods:**

The EUROPA (EvalUation of RObotic partial PAncreatoduodenectomy) trial is designed as a randomised controlled unblinded exploratory surgical trial with two parallel study groups. A total of 80 patients scheduled for elective PD will be randomised after giving written informed consent. Patients with borderline or non-resectable carcinoma of the pancreatic head as defined by the National Comprehensive Cancer Network guidelines, distant metastases or an American Society of Anaesthesiologists (ASA) score > III will be excluded. The experimental intervention, RPD, will be compared with the control intervention, OPD. An intraoperative dropout of approximately eight patients per group is expected because they may receive another type of surgical procedure than planned. Overall, 64 patients need to be analysed. The primary endpoint of the trial is overall postoperative morbidity within 90 days after index operation, measured using the Comprehensive Complication Index (CCI). The secondary endpoints include the feasibility of recruitment and assessment of clinical, oncological and safety parameters and quality of life and cost-effectiveness.

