### Trial design

EUROPA is an investigator-initiated, exploratory, open-label RCT with two parallel study groups.

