#### Analysis variables and statistical methods

The primary endpoint is the CCI within 90 days after the intervention. As a primary result, the 95% CI for the difference in the means between the two groups will be reported. Since the CCI is approximately normally distributed [25], the 95% CI can be computed by means of the normal distribution. Further descriptive measures are reported in terms of mean and standard deviation.

Data analysis will be based on three analysis sets. The intention-to-treat (ITT) set comprises all patients in the group to which they were randomised (converted patients remain in the RPD group) and serves as the primary analysis set. Patients that receive an operation other than PD or total pancreatectomy (explorative laparotomy, diagnostic laparoscopy, etc.) are excluded from further analysis and proceed directly to the end-of-study visit (V8). The per-protocol (PP) set consists of all patients treated per protocol without major protocol violation and without conversions. No missing data will be imputed in the PP set. In addition, the as-treated set will be analysed, which considers the patients in the group in which they were finally treated (i.e. converted patients in the OPD group). There is no evidence that the converted patients will have a higher postoperative CCI than those patients randomised to and remaining in the OPD group. Therefore, and due to the exploratory character of this trial, the as-treated set is an important complement to the ITT and PP sets in this trial.

The primary endpoint is expected to be missing for a small number of patients, since it is objective and short term. In these cases, the primary endpoint is imputed using mean imputation based on the treatment group. As sensitivity analyses, worst-case and best-case scenarios are investigated. Missing values of the primary endpoint will be imputed using the lowest and the highest value of the corresponding treatment group.

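### The planning interval of [3.07, 16.93] is too narrow by a factor of √2: with 32 patients per group and SD 20, the 95% CI around a difference of 10 is about [0.2, 19.8]

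*Protocol article*

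**What the plan says.** The Sample size calculation section states that no formal calculation was made because the trial is exploratory. It then offers an expected precision instead. Its inputs are that "a clinically relevant mean difference for the CCI is 10" and that "the mean standard deviation is approximately 20 in major abdominal surgery". The number analysed is given as "Including 64 patients (32 per group) in the analysis", and the result is that "this effect size could be estimated with a 95% confidence interval (CI) of [3.07, 16.93". The section then adds about eight patients per group for operations that turn out not to be a PD, which brings the number to be randomised to 80. The Abstract (Methods) repeats the target: "Overall, 64 patients need to be analysed".

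Two other sections fix what the interval refers to. Under Trial design, "EUROPA is an investigator-initiated, exploratory, open-label RCT with two parallel study groups". Under Analysis variables and statistical methods, the primary result is defined: "the 95% CI for the difference in the means between the two groups will be reported". The same section says that "the 95% CI can be computed by means of the normal distribution".

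**The concern.** The printed interval has a half-width of 6.93. With an SD of 20 this is what one obtains from a single mean of 32 observations, yet the quantity of interest is a difference between two means of 32 observations each. The sampling variance of the second group appears to be missing.

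The stake is the stated rationale for the trial's size. In an estimation trial, the expected width of the CI plays the part that power plays in a confirmatory trial, and here it is the only figure offered. As printed, it tells the reader that an observed difference of 10 would be estimated well clear of zero. If the half-width is really about 10, the interval around that same difference reaches down almost to zero. The Discussion makes a multicentre confirmatory trial depend on promising results, so those who judge the results would start from a wrong expectation of precision.

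**Working it through.** **Inputs** (Protocol article):
- difference 10, SD 20, 32 per group, 95% level: Sample size calculation
- two independent parallel groups: Trial design
- CI for a difference in means, normal quantile (z = 1.96): Analysis variables and statistical methods
- the SD of 20 is read as common to both groups, since only one value is given

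**Step 1. Reproduce the printed figure.**
Half-width = 16.93 − 10 = 6.93, so the implied SE = 6.93/1.96 = 3.536.
20/√32 = 3.536, and 1.96 × 3.536 = 6.93, giving [3.07, 16.93].
The printed interval is matched to two decimals by the standard error of one mean with n = 32. The same number arises from 20 × √(2/64), which is a two-group formula with 64 entered as the size of each group.

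**Step 2. Compute the interval for the stated design.**
SE = 20 × √(1/32 + 1/32) = 20 × 0.25 = 5.0.
Normal quantile: 10 ± 1.96 × 5.0 = 10 ± 9.80, giving [0.20, 19.80].
t quantile on 62 df (1.999): 10 ± 9.99, giving [0.01, 19.99].
Ratio of half-widths: 9.80/6.93 = 1.414 = √2.

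**Step 3. Look for a reading that would rescue the printed interval.**

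| Variant (SD 20) | Interval |
|---|---|
| 32 per group, 95%, normal | [0.20, 19.80] |
| 32 per group, 95%, t | [0.01, 19.99] |
| 32 per group, 90%, normal | [1.78, 18.22] |
| 32 per group, 80%, normal | [3.59, 16.41] |
| 40 per group (all 80 randomised), 95%, normal | [1.23, 18.77] |
| one sample of 64, 95%, normal | [5.10, 14.90] |

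None gives [3.07, 16.93]. With 32 per group, a half-width of 6.93 would need one of the following: an SD of about 14.1 (3.536/0.25), a confidence level of about 83%, or paired data with a correlation of about 0.5. The article states none of these.

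**Step 4. Sensitivity to the SD (32 per group, 95%, normal).**
SD 15: 1.96 × 15 × 0.25 = ±7.35. SD 25: 1.96 × 25 × 0.25 = ±12.25.
Even an SD of 15 gives a wider interval than the one printed.

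**Step 5. What the printed precision would require.**
n per group = 2 × (1.96 × 20/6.93)² = 64, so 128 analysed. At the article's dropout of 16 in 80 (20%), 128/0.8 = 160 randomised.

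**Step 6. For orientation only, since no test is planned.** If the true difference is 10 and the SD 20, the chance that the 95% CI lies above zero is Φ(10/5.0 − 1.96) = Φ(0.04) = 0.52. The printed SE would imply Φ(10/3.536 − 1.96) = Φ(0.87) = 0.81.

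**The case against.** The strongest defence is that little hangs on the figure. The trial is exploratory and all its analyses are declared descriptive. The reported CI will be computed from the observed data, so a planning error cannot bias it. The stated aims of learning about recruitment, the target population and the variability of morbidity do not depend on the CI excluding zero, and the article does not define promising results by such a rule. The 52% and 81% above describe a test that nobody intends to run. All of this is right, and it limits the consequence to the stated precision and the rationale for 64 patients. It does not make the printed interval correct.

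A second point concerns the cause. Because 20/√32 and 20 × √(2/64) are the same number, one cannot tell whether a one-sample formula was used or 64 was entered as the group size. This stands, and the cause should not be asserted. The size of the error is the same in either case. It does bear on the remedy: if the half-width of 6.93 was itself the target, then 64 analysed patients do not deliver it, and the size needs its own justification.

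Lastly, the SD of 20 and the total of 64 are not errors in themselves. The first is an input, and the second is the number that the interval is meant to support. The step from 64 analysed to 80 randomised is consistent.

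**Conclusion.** The concern holds. For the design, SD and numbers that the article itself gives, the expected 95% CI around a difference of 10 is [0.20, 19.80], not [3.07, 16.93]. The stated half-width is too small by a factor of √2: 6.93 against 9.80, so the true one is 41% wider. This rests on independent groups of 32 and a common SD of 20, both taken from the article. Using t instead of the normal quantile moves the limits by only about 0.2. The expected half-width is as large as the difference regarded as clinically relevant, so the trial can barely separate no difference from a difference of 10. The figure must be corrected because it is the sole quantitative support for the trial's size. The planned analysis remains valid.

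**What to change.** In the Sample size calculation section, replace the interval with [0.2, 19.8] (or [0.0, 20.0] if t is used) and state that 32 patients per group give an expected half-width of about ±10 CCI points at an SD of 20. Add a short statement that the sponsor accepts this precision for an exploratory trial. If the half-width of 6.93 was a real requirement, the size has to be justified anew. Carry the same figure into the full protocol and the SAP if they repeat the interval.

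The cost is a sentence or two and a correction note to the article. The correction itself needs no extra patients and no change to the analysis. The price is that the stated precision looks less favourable.
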